### Data collection

To acquire data on secondary outcomes, we will use face-to-face interviews and questionnaires. At baseline (T0) and after completion of TB treatment (T1; follow-up), all patients in both groups will be asked to complete questionnaires.

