### Outcomes and additional measurements

The primary outcome will be the TB treatment result as defined by the WHO, as follows: Cured, Treatment completed, Treatment failed, Died, Lost to follow-up, Not evaluated, or Treatment success (details available at https://www.ncbi.nlm.nih.gov/books/NBK214446/table/annex2.t1/?report). The secondary outcome will be treatment adherence, defined as the percentage of patients receiving TB treatment who omitted less than 5% of their doses. We will also assess self-reported adherence using the Morisky, Green, and Levine Adherence Scale (MGLS), and we will explore whether the respondents know that TB can affect quality of life (QOL). In the control group, the percentages of patients receiving TB treatment who omit fewer than 5% of their doses by the end of treatment, will be determined by the village physicians.

The “knowledge” variable will be assessed by determining whether the patient can correctly answer 10 questions after having been appropriately educated. QOL refers to general wellbeing, including the ability to balance the negative and positive features of life. Life satisfaction includes physical health status, the family situation, educational attainment, employment status, wealth, religious beliefs, the financial situation, and the environment. The EuroQol five dimensions (EQ-5D) module will be used to assess QOL.

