Each day, the patients will photograph themselves taking their medication using a smartphone; these photographs will be automatically sent to the control center, where the photographs will be assessed. TB patients in the interventional group will receive TB-relevant education from the research term, delivered via the smartphones. Patients with TB in the control group (thus, not following the BSDOT strategy) will be treated according to WHO recommendations; a physician must observe the ingestion of TB treatment pills on 6 days per week. Otherwise, patients in the control group will not receive any additional intervention. Research staff will record the following baseline factors: sociodemographic characteristics including age, sex, socioeconomic status, educational level, marital status, and health behaviors (smoking or drinking status). These baseline data will be used to test the accuracy of randomization and to control for confounding effects on primary and secondary outcomes. The patients in the control group also receive TB education, although it generally comes from village physicians or media sources such as newspaper articles or television broadcasts. Pill consumption frequencies by control groups will be assessed by the village physicians during the 2-week follow-up visits. Some drugs may cause adverse effects such as such as vomiting and diarrhea. Any reports of such conditions require careful analysis; it may be possible to adjust the drug dosage or to avoid taking medication on an empty stomach. Also, it may be useful to regularly measure liver and kidney functions. Treatment may be terminated if the adverse effects are very severe. However, prior to study commencement, patient education in terms of drug effects, dose susceptibilities, and possible adverse effects is essential

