### Statistical analyses

Descriptive statistics will be calculated by reference to baseline data, to allow among-group comparisons. The baseline data will include age, sex, educational level, income, place of birth, smartphone access status, substance use status, distance from home to the nearest county hospital, disease status, and comorbidities. We will compare baseline patient characteristics between the two groups using the chi-squared test or adjusted logistic regression as appropriate. The significance level will be set at *p* ≤ 0.05.

Primary outcomes will be analyzed with the aid of a generalized mixed-effects model featuring both binomial distribution and logistic regression. Randomization (the intervention/control comparison) will serve as an independent variable. To accommodate the clustered design, we will treat clustering as a random effect. Potential confounders (age, sex, socioeconomic status, and other features) differing significantly between the intervention and control groups will be treated as fixed factors. Secondary outcomes (adherence to the medication regime, and education in terms of TB and QOL) will be explored with the aid of generalized linear mixed-effect models employing logistic or linear regression, as appropriate. Secondary outcome modeling will include baseline assessments as covariates. We will report all descriptive and inferential statistics with their 95% confidence intervals [23, 24]. We will treat TB treatment outcomes, treatment adherence, and self-reported adherence as enumerative data. Missing data will be handled by a complete case analysis which excludes individuals with missing data.

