### Cost-effectiveness of the intervention

Addressing whether the program is cost-effective is also an important consideration for the trial. Our cost-utility analysis will assess the cost per quality-adjusted life-years (QALYs) that were added to the patient’s life as a result of the program. This analysis takes a societal perspective, such that any cost to any stakeholder is accounted for including volunteer time. The lower the cost per QALY is, the more cost-effective the program becomes. In the present study, costs of TB treatment, and those of control of relevant symptoms (e.g., village physicians’ time and medications), will be weighed against costs not incurred (those of hospitalization and the social costs incurred by the disruption of village life). The costs and savings afforded by the proposed study can be compared to those of other medical interventions. We will estimate costs using a Markov chain approach.

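### The T1 questionnaires are promised for all patients but timed by completion of treatment, so patients who stop or default have no defined T1

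*Protocol article*

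**What the plan says.** The Data collection section sets two questionnaire times. T0 is baseline. T1 is described thus: "after completion of TB treatment (T1; follow-up), all patients in both groups will be asked to complete questionnaires". No calendar time, window or rule for patients who leave treatment early is attached to T1. The same section says what the questionnaires are for: "To acquire data on secondary outcomes, we will use face-to-face interviews and questionnaires".

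Under Outcomes and additional measurements, the measures that depend on asking the patient are:
- self-reported adherence: "We will also assess self-reported adherence using the Morisky, Green, and Levine Adherence Scale (MGLS")
- knowledge, judged by "whether the patient can correctly answer 10 questions after having been appropriately educated"
- quality of life: "The EuroQol five dimensions (EQ-5D) module will be used to assess QOL"

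The protocol expects that not every patient completes. Its primary outcome categories include failure, death and loss to follow-up, and Individual-level interventions states: "Treatment may be terminated if the adverse effects are very severe".

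The Statistical analyses section says: "Missing data will be handled by a complete case analysis which excludes individuals with missing data".

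The Phase 3 description under Study sites follows all participants for 6 months with monthly check-ups, but Data collection does not link T1 to the end of that period.

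**The concern.** Within one sentence the protocol says who is asked (everyone) and when (once treatment is complete). For a patient whose treatment is terminated, or who defaults, the second part never happens, so staff who follow the text have no date on which to approach that patient. Under the complete-case rule, a patient without T1 leaves the analysis.

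This matters because treatment success, which overlaps heavily with completion, is what the intervention is designed to raise. If missing T1 data follow non-completion, the two analysed groups have been selected after randomisation by an event that the intervention changes. More patients would be expected to drop out of the control arm, probably those with poorer adherence and quality of life. A benefit on MGLS or EQ-5D could then be understated. An analysis plan written later cannot recover questionnaires that were never given.

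**Working it through.** **Step 1. Can T1 be dated from the text?**
- *Completes treatment:* yes, after completion, although no window is given.
- *Stops treatment or defaults:* no, because the trigger never occurs.
- *Treatment fails:* unclear. The document does not say whether such a patient counts as having completed.
- *Dies, or is truly lost:* no T1 under any schedule.

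The 6-month follow-up could serve as a common date, but the text does not say so. The two times cannot be assumed to coincide: the Recruitment section puts the continuation phase alone at about 6 months on average.

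**Step 2. How many patients could be affected, at most?** The article gives no rate of non-completion. The nearest figures are in Sample size: success of 0.78 under usual care and a planned increase of 0.15.
- Intervention success: 0.78 + 0.15 = 0.93.
- Without success: 1 − 0.78 = 22% of controls; 1 − 0.93 = 7% of intervention patients.
- With 1300 patients allocated 1:1 (650 per arm): 0.22 × 650 = 143 controls; 0.07 × 650 = 45.5, about 46, intervention patients.
- Overall: (143 + 45.5) / 1300 = 14.5%.

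This is a ceiling for loss through not completing. It treats every patient without success as having no T1, which the document does not say. The loss due to the timing rule lies between 0 and these numbers. For scale, Sample size allows 5% for missing data, but on the trial endpoint rather than on the questionnaires.

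**Step 3. What could the selection do?** This is an illustration only, since the adherence rates are assumed. Let MGLS adherence be *a* in patients with treatment success and *b* in the others, the same in both arms.
- All-patient difference = (0.93*a* + 0.07*b*) − (0.78*a* + 0.22*b*) = 0.15(*a* − *b*).
- Difference among successes only = *a* − *a* = 0.

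With *a* = 0.90 and *b* = 0.20:
- controls: 0.78 × 0.90 + 0.22 × 0.20 = 0.746
- intervention: 0.93 × 0.90 + 0.07 × 0.20 = 0.851
- difference: 10.5 points in all patients, against 0 in successes only

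With *a* = 0.90 and *b* = 0.50: 0.812 v 0.872, a difference of 6.0 points against 0.

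If only half of the patients without success lack T1 (*a* = 0.90, *b* = 0.20):
- controls: (0.702 + 0.20 × 0.11) / (0.78 + 0.11) = 0.724 / 0.890 = 81.3%
- intervention: (0.837 + 0.20 × 0.035) / (0.93 + 0.035) = 0.844 / 0.965 = 87.5%
- difference: 6.1 points, against 10.5 in all patients

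The zero among successes is built in by giving both arms the same *a*. If the intervention also raises adherence among successes, the difference there is not zero. If *a* = *b*, there is no distortion. The all-patient figures also give an MGLS value to patients who died or were lost, so no schedule could recover the whole gap.

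**The case against.** The strongest objection is that the sentence itself says all patients in both groups are asked, that it labels T1 as follow-up, and that everyone is followed for 6 months. A natural reading is baseline and end of the treatment period, for everyone. That is a fair reading, and it rules out a stronger one that a reader might infer, namely that these outcomes will compare completers only. Nothing in the document restricts T1 to completers. What remains is that the wording gives non-completers no date.

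A second objection is that a journal article may leave visit windows to a full protocol. That holds for a missing window. Here, however, the article does state the trigger for T1, and the stated trigger is the difficulty.

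Third, two further inferences go too far:
- *That the adherence outcome as a whole is compromised.* The named secondary outcome, omission of less than 5% of doses, is assessed at 2-week visits in both arms and does not depend on T1.
- *That the cost-utility result is biased.* The protocol says: "Our cost-utility analysis will assess the cost per quality-adjusted life-years (QALYs) that were added to the patient’s life". It gives no source for the utilities. EQ-5D is the only quality-of-life instrument named, so the link is plausible but not stated.

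Fourth, the complete-case rule is what removes patients from the analysis, and it can be questioned in its own right. The timing of T1 is still a separate matter, because it decides whether the data exist at all.

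Finally, a fixed date can catch some patients on treatment and others after it. That is a real cost, and it is the same in kind in both arms.

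**Conclusion.** The point stands as an internal inconsistency with a risk of bias, not as a demonstrated bias. T1 is promised to all patients but timed by an event that some never reach. Together with complete-case analysis, this risks arm-dependent selection in MGLS, knowledge and EQ-5D, and in the QALYs if EQ-5D supplies the utilities. The primary outcome and dose-based adherence are not touched.

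The size cannot be derived from the document. The 22% v 7% ceiling rests on equating lack of success with lack of T1. The part that a better schedule can recover is smaller: patients who stopped, defaulted or failed but can still be reached. The point gaps in the working depend on assumed adherence rates and should not be quoted as estimates. The change is worth making because it is cheap and cannot be made retrospectively.

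**What to change.** Reword Data collection along these lines: T1 is done at one fixed time after enrolment, the same in both arms, for every living, reachable patient, whether or not TB treatment was completed. The end of the existing 6-month follow-up is one candidate. Add that stopping treatment or the bracelet is not withdrawal from follow-up.

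The cost is the protocol wording plus calls or visits to trace patients who have left treatment; the monthly check-ups already provide a structure for this. The downside is that for some patients T1 will fall shortly before or after the end of treatment, so the date of T1 relative to the end of treatment should be recorded. Deaths and true losses will still lack T1, and the report should count them by arm.

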### Blinding

Participating village physicians and patients with TB cannot be blinded; the BSDOT intervention features open participation. We will blind the research group members involved in data analysis.

### Data management

After the survey is completed, all questionnaires will be checked by one staff member in terms of missing information, unusual responses, and erroneous data. Two staff members will load all data into an SPSS (Statistical Product and Service Solutions, Version 21.0) database; the two databases will then be reconciled to minimize data entry-related errors.

### Statistical analyses

Descriptive statistics will be calculated by reference to baseline data, to allow among-group comparisons. The baseline data will include age, sex, educational level, income, place of birth, smartphone access status, substance use status, distance from home to the nearest county hospital, disease status, and comorbidities. We will compare baseline patient characteristics between the two groups using the chi-squared test or adjusted logistic regression as appropriate. The significance level will be set at *p* ≤ 0.05.

Primary outcomes will be analyzed with the aid of a generalized mixed-effects model featuring both binomial distribution and logistic regression. Randomization (the intervention/control comparison) will serve as an independent variable. To accommodate the clustered design, we will treat clustering as a random effect. Potential confounders (age, sex, socioeconomic status, and other features) differing significantly between the intervention and control groups will be treated as fixed factors. Secondary outcomes (adherence to the medication regime, and education in terms of TB and QOL) will be explored with the aid of generalized linear mixed-effect models employing logistic or linear regression, as appropriate. Secondary outcome modeling will include baseline assessments as covariates. We will report all descriptive and inferential statistics with their 95% confidence intervals [23, 24]. We will treat TB treatment outcomes, treatment adherence, and self-reported adherence as enumerative data. Missing data will be handled by a complete case analysis which excludes individuals with missing data.

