### Recruitment

The village physicians treating patients in both groups will be trained to collect and report all new and previously treated drug-sensitive cases of TB. Our research staff (who have professional medical knowledge) will be trained on the protocols and procedures of the study and will initially contact eligible patients after (1) village physicians identify patients who meet the study criteria, (2) eligible patients have been contacted by telephone, (3) patient eligibility has been confirmed, (4) the research project has been explained to patients with TB by telephone, patient consent has been gained, and contact information recorded, and (5) interviews have been arranged between patients with TB and other research staff. The research staff will also ask patients about their smartphone usage and the number of smartphones in the household. The average duration of the continuation phase of drug-sensitive TB treatment will be about 6 months.

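### Covariates for the primary model are chosen by baseline significance tests from an open list, instead of being fixed in advance for their prognostic value

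*Protocol article*

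**What the plan says.** The rule is in the protocol article under Statistical analyses. Baseline characteristics are tested first: "We will compare baseline patient characteristics between the two groups using the chi-squared test or adjusted logistic regression as appropriate". A difference counts as significant when p ≤ 0.05. The result then decides the primary mixed logistic model: "Potential confounders (age, sex, socioeconomic status, and other features) differing significantly between the intervention and control groups will be treated as fixed factors". The same section deals with clustering in the outcome model ("To accommodate the clustered design, we will treat clustering as a random effect") and says nothing equivalent about the baseline tests.

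The candidates begin: "The baseline data will include age, sex, educational level, income, place of birth, smartphone access status, substance use status". The list goes on to distance to the county hospital, disease status and comorbidities, which makes ten variables. Under Individual-level interventions there is a second, different list, which includes marital status and smoking or drinking. It carries the same purpose: "These baseline data will be used to test the accuracy of randomization and to control for confounding effects on primary and secondary outcomes".

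No section names a covariate that always enters the primary model. The secondary models, by contrast, always include the baseline assessments.

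**The concern.** This is a rule that the article states, not a detail left to an analysis plan that is not shown. It has two faults.

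- **It selects on the wrong property.** Adjustment is worth most for variables that predict outcome. A between-arm p-value measures imbalance only. A strong predictor that is balanced is left out, and an irrelevant variable that is imbalanced by chance is put in.
- **It leaves the primary model open.** The covariates depend on the observed data, and the rule's reference to other features does not close the list. Two analysts could reach different primary models under the same text.

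At stake are the precision of the primary comparison and the claim that the primary analysis was fixed beforehand.

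**Working it through.** The plan gives no figure for this rule, so there is none to reproduce. The checks below measure how often the rule selects by chance and what that costs.

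**Inputs from the article.** Ten listed variables and p ≤ 0.05 (Statistical analyses). Seven clusters per arm, 1300 patients before the missing-data allowance, and an outcome ICC of 0.1 (Sample size).

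**Inputs assumed.** Independence of the ten tests, and covariate ICCs of 0.01 to 0.1. The article gives no ICC for any baseline variable.

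**1. Valid 5% tests.** P(at least one flag among ten) = 1 − 0.95^10 = 0.401. The expected number of flags is 10 × 0.05 = 0.5.

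**2. Whole clusters randomised, chi-squared test ignoring clustering.** Cluster size m = 1300/14 = 92.9. Design effect DE = 1 + (m − 1) × ICC. Flag rate for a variable with no true imbalance = 2 × [1 − Φ(1.96/√DE)].

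| Assumed covariate ICC | DE | Flag rate per variable | Expected flags among ten |
|---|---|---|---|
| 0.01 | 1.92 | 0.157 | 1.6 |
| 0.02 | 2.84 | 0.245 | 2.5 |
| 0.05 | 5.59 | 0.407 | 4.1 |
| 0.1 | 10.19 | 0.539 | 5.4 |

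A beta-binomial simulation of a variable with 50% prevalence (20,000 runs) gave 0.157, 0.400 and 0.537 at ICC 0.01, 0.05 and 0.1.

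**3. Patients allocated within county.** The same kind of simulation gave flag rates of 0.037 to 0.049, so the test is not inflated. Over ten independent variables, the lowest and highest simulated rates give 1 − (1 − 0.0369)^10 = 0.31 and 1 − (1 − 0.0485)^10 = 0.39. Any selection is still by chance.

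**4. Consequence for the primary comparison.** An illustrative simulation used 6,000 runs, 14 clusters of 93, a continuous outcome and one binary covariate with an effect of 1 residual SD. Arms were compared by a t-test on cluster means. Every effect size here is assumed.

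| Covariate ICC | Quantity | Always adjust | Test, then adjust | Never adjust |
|---|---|---|---|---|
| 0.1 | Type I error | 0.049 | 0.041 | 0.053 |
| 0.1 | Power | 0.90 | 0.87 | 0.82 |
| 0.02 | Type I error | 0.049 | 0.045 | 0.048 |
| 0.02 | Power | 0.90 | 0.89 | 0.885 |

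The rule left out this strongly prognostic covariate in 46% of runs at ICC 0.1 and in about 75% at ICC 0.02.

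**The case against.** The strongest objection concerns the clustering figures in step 2. They need whole clusters of about 93, randomised seven per arm. Study sites selects only seven counties and can be read as placing patients from each county in both arms, in which case the inflation disappears. If villages are the clusters, the listed counts sum to 150 + 340 + 288 + 314 + 140 + 327 + 462 = 2,021 villages for 1,365 patients. That is fewer than one patient per village on average, and a design effect near 1. The ICC of 0.1 is a planning value for the outcome, and the logistic alternative to the chi-squared test is undefined and might allow for clusters. All of this stands, so the 16% to 54% range is conditional.

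A reader might also infer stronger harms that the documents and calculations do not support:

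- **Inflated type I error.** The simulated rate under the rule was 0.041 or 0.045, below 0.05.
- **An overloaded model.** With 650 per arm, 22% unsuccessful under control and 13.2% or 7% under intervention, events number 143 + 86 = 229 or 143 + 45.5 = 188.5. That is roughly 19 to 23 per term even if all ten variables entered as single terms.
- **Treatment history collected but ignored.** Recruitment says that physicians report "all new and previously treated drug-sensitive cases of TB". This describes which cases are reported. Neither baseline list names treatment history as a recorded variable.

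There is also a case for looking at baseline balance. Unblinded village physicians identify patients in both groups, so if clusters are randomised, recruitment could differ by arm. That justifies describing the arms side by side; it does not make a p-value a sound way to choose covariates. Blinding the analysts limits deliberate choice but does not fix the model in advance.

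**Conclusion.** The concern holds for the selection rule itself. The primary covariates depend on chance imbalance, from an open list, and prognostic strength plays no part. With valid tests and ten independent variables, the chance of at least one such selection is about 40%. A higher rate applies only if whole clusters are randomised and the baseline test ignores clustering, and its size then rests on assumed covariate ICCs.

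The demonstrated harm is a data-dependent model and a modest loss of precision. Under strong assumed prognosis, power fell from 0.90 to 0.87 at covariate ICC 0.1 and to 0.89 at 0.02. That illustration used a continuous outcome and cluster means, not the planned logistic mixed model, so it shows direction and rough size only. It would be wrong to conclude that the trial's error rate is unprotected or that half of the balanced variables will certainly be flagged. The rule should be changed because a better one is available at almost no cost.

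**What to change.** Replace the selection sentence before the analysts are unblinded:

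- Name a short set of prognostic covariates from the variables already listed, for example age, sex, disease status and comorbidities. Include them in the primary mixed model whatever the baseline p-values, and remove the open-ended wording.
- Report baseline characteristics by arm descriptively. Delete the significance tests and the stated aim: "These baseline data will be used to test the accuracy of randomization".
- Show the unadjusted estimate as a sensitivity analysis.
- Add new versus previously treated status only if it is confirmed to be recorded.
- Enter county as a stratum if patients are allocated within county, or as the random cluster effect if counties are the randomised unit. The article must first state which unit is randomised.

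The cost is a few sentences. The example covariates are already on the plan's baseline list, and the sample size, alpha and stated power are unaffected.

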### Assignment to the intervention and control groups

In the intervention group, after signing the Informed Consent Form, each participant will be provided with a bracelet, a battery charger, medication, and a smartphone. The village physicians will insert 2 weeks’ worth of medication into the bracelet, tell participants how to use the bracelet, and explain how to refill the bracelet after 2 weeks. Baseline participant information will be collected via structured questionnaires. Participants will use the bracelets for 6 months. The control group will receive neither the bracelet nor the mobile application; rather, they will receive a traditional TB treatment regimen under the DOT strategy, which includes the same medications as the intervention group. The intervention group’s medication adherence will be assessed using the BDOT strategy, while participants in the control group will visit the physicians for treatment under direct observation. Pill consumption will be assessed by the village physicians during follow-up visits scheduled at 2-week intervals.

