### Sample size

Sample size calculations were based on a cluster randomized trial; the endpoint was the nonrecovery rate at the end of the trial. Assuming seven clusters per arm, a two-sided type-I error of 5%, a type-II error of 10%, and a percentage with nonadherence in the control arm of 30%, an intra-cluster correlation coefficient (ICC) of 0.1 was estimated as a mid-range value from a list of ICCs from similar studies in terms of intervention targets, outcomes, and units of randomization. Using a treatment effect size of a 0.15 increase in the proportion of successful treatments over the 0.78 successful treatment rate for usual care, based on published local treatment success rates and findings of studies with a smartphone as a facilitator of adherence in similar settings, 1300 TB patients would be required to detect a 40% reduction in the endpoint in the intervention arm with an alpha of 0.05, power of 90%, and coefficient of variation of 0.25. The sample size was adjusted to 1365 assuming 5% missing endpoint data.

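### The complete-case rule is not limited to outcomes, so a patient with a known treatment result can be dropped for a blank baseline item

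*Protocol article*

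**What the plan says.** All of the following comes from the Protocol article.

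- **Missing-data rule (Statistical analyses):** "Missing data will be handled by a complete case analysis which excludes individuals with missing data". No other method or sensitivity analysis for missing data is given.
- **Primary model (Statistical analyses):** "Potential confounders (age, sex, socioeconomic status, and other features) differing significantly between the intervention and control groups will be treated as fixed factors".
- **Secondary models (Statistical analyses):** "Secondary outcome modeling will include baseline assessments as covariates".
- **Baseline items (Statistical analyses):** "The baseline data will include age, sex, educational level, income, place of birth, smartphone access status, substance use status", followed by distance to the county hospital, disease status and comorbidities. That makes ten items, listed for description and for comparing the groups.
- **Source of baseline data (Assignment to the intervention and control groups):** "Baseline participant information will be collected via structured questionnaires".
- **Allowance for loss (Sample size):** "The sample size was adjusted to 1365 assuming 5% missing endpoint data".
- **Primary outcome categories (Outcomes and additional measurements):** "Cured, Treatment completed, Treatment failed, Died, Lost to follow-up, Not evaluated, or Treatment success".

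**The concern.** The rule refers to individuals with missing data of any kind. Once a model contains questionnaire covariates, a blank on one of them removes the patient, whatever is known about the treatment result. This is a different matter from how patients who are lost or not evaluated are scored: here the outcome is in hand and is set aside because of a covariate.

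Two things are at stake. The first is an avoidable loss of patients that the sample size does not provide for. The second, and more important, is who is analysed. Patients who answer questions on income or substance use may differ from those who do not. If only blanks in modelled covariates count, the primary analysis set also depends on which items pass a significance screen. Adjusted and unadjusted results could then differ because the patients differ, and the secondary models could each cover a different group.

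**Working it through.** **1. The plan's own allowance.** From the Sample size section: 1300 patients before the allowance, 5% missing endpoints, 1365 after. 1300 x 1.05 = 1365, so the step reproduces. (Dividing instead gives 1300 / 0.95 = 1369 after rounding up.) If 5% of endpoints are missing, 1365 x 0.95 = 1297 patients remain. Nothing in this step is for blank baseline items.

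**2. Loss from blank covariates.** Let j be the number of modelled covariates and q the share of patients with a given item blank. If blanks are independent, the share dropped is 1 - (1 - q)^j, and the number analysed is 1296.75 x (1 - q)^j. Both q and j are assumptions.

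| q | j = 3: dropped (analysed) | j = 5: dropped (analysed) |
|---|---|---|
| 1% | 3.0% (1258) | 4.9% (1233) |
| 2% | 5.9% (1220) | 9.6% (1172) |
| 3% | 8.7% (1184) | 14.1% (1114) |

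Independence gives a larger loss than overlapping blanks. If the same patients leave every item blank at 3%, the loss is 3% for any j: 1297 x 0.97 = 1258.

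**3. Why three to five covariates is plausible.** The baseline comparison is to use chi-squared tests or logistic regression, with no mention of clustering. Suppose whole clusters are allocated, 14 in all, with 1365 / 14 = 97.5 patients each. For assumed covariate intra-cluster correlations of 0.02, 0.05 and 0.10, the design effects 1 + 96.5 x ICC are 2.9, 5.8 and 10.7. A test that ignores clustering then flags a chance difference with probability 2 x [1 - Phi(1.96 / sqrt(design effect))], which is about 25%, 42% and 55%. Of ten items, roughly three to five would enter the model.

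**4. Effect on power.** Inputs from the Sample size section: seven clusters per arm, two-sided 5%, coefficient of variation 0.25, control rate 0.30, and a 40% reduction, so 0.30 x 0.6 = 0.18. With m = N / 14, the Hayes-Bennett variance is

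[(0.30 x 0.70 + 0.18 x 0.82) / m + 0.25² x (0.30² + 0.18²)] / (7 - 1),

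and power is Phi(0.12 / sqrt(variance) - 1.96).

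- N = 1297: m = 92.6, variance = (0.00386 + 0.00765) / 6 = 0.00192, power 0.782.
- N = 1114 (five covariates, 3% blank): power 0.760.
- N = 1003 (five covariates, 5% blank, beyond the range above): m = 71.6, variance = (0.00499 + 0.00765) / 6 = 0.00211, power 0.744.

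The between-cluster term, 0.00765, does not shrink with more patients, so losing patients changes little. With the section's other inputs (success 0.78 rising by 0.15, so non-success 0.22 to 0.07), power goes from 0.998 at 1297 to 0.995 at 1003. With the stated ICC of 0.1 in place of the coefficient of variation, it goes from 0.353 to 0.346 for 0.30 versus 0.18. That these levels do not match the planned 90% is a separate matter; only the change with N bears on this point.

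**The case against.** The strongest reply is that the loss may be small. The ten-item list serves description and group comparison, while the primary model takes only items that differ significantly, possibly none. Age and sex will rarely be blank, research staff record the sociodemographic factors, and Data management provides for checking questionnaires for blanks. All of this stands as a limit on size. The check comes after the survey, however, so recovery of blanks is not assured.

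A reader might infer a loss of 9.6%, 18.3% or 26.3%, from ten covariates each 1%, 2% or 3% blank. The protocol does not specify a ten-covariate model. On the most literal wording, a blank in any collected item would exclude the patient, but the analysis set would then be fixed and would not vary with the covariates. The larger loss and the shifting set should not be claimed together.

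A reader might also infer that the rule is what pushes the trial below its required 1300. It is not: 1297 is already below 1300 without any covariate loss. Moreover, loss to follow-up and non-evaluation are themselves outcome categories. If they are scored, few endpoints are missing and the 65 extra patients absorb some of the loss. With no endpoints missing and three covariates 1% blank, 1365 x 0.97 = 1324 remain. The plan does not provide for this use of the 65, but it could happen.

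Finally, handling of missing covariates is often left to an analysis plan, and choosing covariates by significance is a root of the instability. Both are fair. But the article does not leave the matter open: it states a rule, and the rule as worded discards known results.

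**Conclusion.** The point holds on the wording of the Statistical analyses and Sample size sections: patients with a known result can be excluded for a blank baseline item, and no allowance is made for it. The size cannot be found from the protocol. About 3% to 14% rests on assumed, independent blanks of 1% to 3% per item and three to five modelled covariates, and it falls if blanks overlap.

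A serious loss of power is a tempting inference, but the plan's own inputs do not support it: even at 1003 patients, power falls only from 0.782 to 0.744 in the 0.30 versus 0.18 case. The main harm is an analysis set that is selected and, on the model-by-model reading, unstable. The protocol gives no basis for stating the direction or size of any resulting bias. The rule should be changed because it is avoidable at almost no cost; it is not a fatal flaw.

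**What to change.** - State that the complete-case rule applies to missing outcomes only.
- Keep every randomised patient with an outcome. Fill blank baseline covariates without using arm or outcome (overall mean for continuous items, a separate missing category for categorical items), or use multiple imputation.
- Report the unadjusted cluster model on the same patients, so that any difference from the adjusted result reflects adjustment alone.
- Report the number of blanks for each covariate by arm.

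Simple filling is generally acceptable for baseline covariates in a randomised comparison, but it should not be described as free of bias in every case. It adjusts only partly for a covariate with many blanks, and it relies on blanks being similar in both arms. That is not assured here: village physicians and patients are unblinded, village physicians identify the patients, and those in the intervention clusters receive extra training in study paperwork. This is why the count by arm is needed.

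The cost is a sentence or two in the analysis section, minor programming and one extra table row per covariate. No new data or visits are needed.
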